## Abstract

**Background:**

The hippocampus is a key brain region for episodic memory, and impairment of episodic memory is the earliest feature of amnestic mild cognitive impairment (aMCI). Preserving the structure and function of the hippocampus plays a key role in preventing progression to Alzheimer’s disease (AD). Therefore, early intervention is crucial, and acupuncture could significantly improve episodic memory in aMCI, but the mechanism is not clear. Accordingly, this experiment aims to explore the mechanism of acupuncture to improve episodic memory in aMCI based on the hippocampal subregion.

**Methods:**

A randomized, controlled, blinded research will be performed. 150 aMCI participants will be assigned to the verum acupuncture group, sham acupuncture group, and waiting group; 50 healthy controls will also be recruited. Patients in the acupuncture group will receive real acupuncture treatment or placebo acupuncture three times per week, 36 sessions over 12 consecutive weeks in total. Patients in the waiting group will receive the same verum acupuncture treatment for compensation after the trials are finished. The primary outcome will be the auditory-verbal learning test. Secondary outcomes will include Montreal Cognitive Assessment (MoCA), Mini-Mental State Examination (MMSE), Hamilton Depression Scale (HAMD), and functional magnetic resonance imaging data. Outcomes will be measured at baseline and 12 weeks after randomization. Repeated measurement analysis of variance will be used to explore the intervention effect.

**Discussion:**

This protocol will provide theoretical support for the neural mechanisms by which acupuncture improves episodic memory in aMCI. We hope that this study will provide objective evidence and offer alternative treatment options for the early treatment of aMCI.

**Clinical trial registration:**

ChiCTR2400084308.

## Introduction

1

Mild cognitive impairment (MCI) refers to a state in which memory loss is greater than aging while cognitive function still remains, a transitional stage between normal cognition and Alzheimer’s disease (AD) (1). Recent epidemiological investigations indicate that the prevalence of mild cognitive impairment (MCI) in China is approximately 15.5%, corresponding to an estimated 38.77 million individuals (2). Advanced age constitutes a significant risk factor for MCI (3). According to the United Nations Department of Economic and Social Affairs, Population Division (4), the global population aged 65 and over is projected to account for nearly 12% by 2030. By 2050, this figure is expected to rise to 16%. Specifically, by 2050, the global population aged 65 and above is anticipated to reach 1.8 billion, constituting 16% of the total population. Meanwhile, the global population aged 60 and above is projected to reach 2 billion by 2050, accounting for 18% of the total population. Consequently, the number of individuals with MCI is expected to exhibit an increasing trend. MCI can be categorized into three subtypes: amnestic mild cognitive impairment (aMCI), multiple domain MCI and single non-memory domain MCI (e.g., language and visuospatial) (5). Previous studies have shown that patients with aMCI are more likely to progress to AD compared to similarly aged and cognitively normal individuals and those with non-aMCI (naMCI) (6, 7). Therefore, it is particularly important to diagnose and intervene early in aMCI and to prevent it from worsening during the aMCI stage.

In recent years, the disease-modifying therapies (DMTs), which aim to restrain the neuropathological progression of AD, have been evolving rapidly. Unfortunately, most drugs based on DMTs have not been put into clinical application or are still in the clinical trial phase (8). Researchers have found that punicalagin in pomegranate may target the underlying mechanisms of MCI and enhance therapeutic outcomes. However, there is no nutritional health therapy with regard to pomegranate to suppress it (9). Therefore, it is crucial to find a safe and effective therapy for the treatment of aMCI.

Recently, acupuncture, as a safe and reliable non-drug therapy, has been fully confirmed for its efficacy in the treatment of cognitive impairment (10–14). Our previous randomized controlled trial (RCT) also proved it can alleviate cognitive symptoms (15). However, the mechanism of acupuncture treating aMCI has not been revealed.

With the development of magnetic resonance imaging (MRI) technology, several studies have shown that the structure and function of specific brain regions are altered in patients with aMCI (16–18). Notably, the hippocampus, as the hub of regions dealing with episodic memory (19), is closely related to the development of aMCI (20). Episodic memory is a declarative memory in which the brain combines the content of an event that triggers an individual’s emotional or ideological awakening with spatio-temporal information to encode and store it (21). Episodic memory belongs to the category of long-term memory, which is an advanced cognitive function possessed by humans. The researchers found that during the formation, object “what,” spatial “where” and temporal “when” of episodic memory were transmitted to the hippocampus through different information flow paths for integrated coding (22) Researchers found that there is a decrease in the volume of the hippocampus and abnormal hippocampal dynamic functional connectivity (dFC) in aMCI, compared to healthy people (23, 24).

Therefore, we hypothesize that acupuncture could enhance episodic memory in aMCI by remodeling hippocampal subregional connectivity and volume, thereby offering a mechanistic basis for its clinical application. Then we designed a randomized controlled trial with the aim of (1) evaluating the efficacy and safety of acupuncture in improving episodic memory in aMCI patients and (2) exploring the structural and functional changes of hippocampal subregion underlying acupuncture’s therapeutic effects.

## Methods

2

### Study design

2.1

This is a prospective, single-center, three-armed, parallel-designed, assessor-blinded, randomized controlled trial. A total of 150 participants with aMCI and 50 healthy controls (HCs) will be enrolled. The 150 eligible patients will be randomly assigned to the verum acupuncture group, the sham acupuncture group, and the waiting group in a ratio of 1:1:1. Healthy volunteers will serve as a comparison group for baseline comparisons. The enrollment schedules, interventions, and assessments are summarized in Table 1. A study flowchart is provided in Figure 1.

**Table 1 tab1:** Schedule of enrollment, intervention, and assessments.

Item	Study period				
	aMCI				Healthy volunteers
	Baseline	Treatment phase			Baseline
	0 week	Week 1	→	Week 12	0 week
Enrollment					
Inclusion criteria	×				×
Exclusion criteria	×				×
Informed consent	×				×
Intervention					
Verum acupuncture group		×	×	×	
Sham acupuncture group		×	×	×	
Control group					
Outcome measurement					
Clinical features					
AVLT-H	×			×	×
MoCA	×			×	×
MMSE	×			×	×
HAMD-17	×			×	×
fMRI					
3DT1WI	×			×	×
T2WI	×			×	×
Flair	×			×	×
rs-fMRI	×			×	×
DTI	×			×	×
Safety					
Adverse events		×	×	×	

**Figure 1 fig1:**
[figure not shown]
Flow chart of the trial procedures.

### Sample size

2.2

The sample size for MRI studies is typically determined by practical constraints such as scanning time, cost, and effect size, so there is no unified standard. Desmond et al. conducted a statistical efficiency analysis based on the estimation of sample size in MRI studies, indicating that approximately 12 participants can achieve 80% power in typical activation at the voxel level (25). After considering that increasing the sample size could significantly enhance the stability of the results and accounting for a certain dropout rate, we therefore decided that each group will include 50 participants, totaling 150 aMCI patients and 50 healthy controls.

### Recruitment

2.3

Participants with aMCI and HCs for this study will be recruited from Shenzhen Traditional Chinese Medicine Hospital. All potential participants will be thoroughly briefed on the objectives, its procedures, potential benefits, and associated risks of the study protocol. Before enrollment, they will be asked to voluntarily sign an informed consent form, signifying their understanding and agreement to participate in the study.

### Eligibility criteria

2.4

#### Inclusion criteria

2.4.1

Patients of aMCI meet the following criteria: (1) diagnosis based on the aMCI diagnostic criteria proposed by Petersen (26); (2) right-handedness; (3) age 50–75 years without limitation of gender; (4) Objective Memory Impairment confirmed Auditory Verbal Learning Test Fifth Trial (AVLT_N5) score > 1 standard deviation (SD) below the age-adjusted normative mean; (5) self-reported memory impairment or cognition complaints by caregivers, with a disease course > 6 months.

Healthy controls meet the following criteria: (1) cognitive integrity confirmed by Mini-Mental State Examination (MMSE) score ≥27 and absence of subjective cognitive complaints; (2) right-handedness; (3) age 50–75 years without limitation of gender.

#### Exclusion criteria

2.4.2

Patients with aMCI who meet any of the following criteria will be excluded: (1) a history of or current diagnosis of neurological or neuropsychiatric disorders that may impair cognitive function (e.g., stroke, epilepsy, major depressive disorder, schizophrenia, or neurodegenerative diseases such as Parkinson’s disease); (2) recent participation in therapeutic interventions (e.g., acupuncture or pharmacotherapy) within the past 4 weeks or concurrent enrollment in other clinical trials; (3) inability to complete neuropsychological assessments or undergo MRI examination due to severe sensory deficits (e.g., aphasia, blindness, hearing loss) or MRI contraindications; (4) clinically significant unstable systemic conditions (e.g., cardiac, hepatic, renal or respiratory diseases); (5) systemic diseases or comorbidities associated with cognitive impairment (severe anemia, HIV infection, untreated thyroid dysfunction, syphilis, alcohol and drug addiction, or anthrax).

Healthy controls meeting following criteria will be excluded: (1) a history of or current diagnosis of neurological, neuropsychiatric, or systemic disorders associated with cognitive impairment (epilepsy, Parkinson’s disease, severe anemia, HIV infection, alcohol or drug addiction, syphilis, or thyroid dysfunction); (2) contraindications to MRI examination; (3) clinically significant unstable systemic conditions (e.g., cardiac, hepatic, renal or respiratory diseases); (4) participation in other clinical trials within the past 6 months.

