Furthermore, in the design of using sham acupuncture as the control group, we will use blunt needles at acupoints rather than non-acupoints. The primary reason is that this study aims to verify the therapeutic mechanism of acupuncture on episodic memory in aMCI patients, not to validate acupoint specificity. Applying blunt needles at acupoints for SA aims to maximally simulate the VA treatment environment (including the operation site, doctor-patient interaction, and sensory experience), thereby more strictly controlling the placebo effect and reducing the risk of unblinding for patients. In fact, regarding acupoint selection, in addition to the 362 conventional acupoints, there are numerous extraordinary acupoints distributed throughout the body. Therefore, it is difficult to find inactive superficial acupoints. Concerning needle insertion methods, both superficial needling and needle withdrawal create some nerve stimulation in the area. This stimulation can then affect related parts of the brain, leading to what are called “edge contact effects,” which is not an inactive placebo (41, 42). Therefore, this finding does not mean that acupoints are unimportant, it shows that the we must carefully consider the placebo effect in acupuncture research.

The main advantages of this study are as follows: first, aMCI patients will be compared with healthy individuals to identify pathological changes in hippocampal subregions. Meanwhile, we will explore how acupuncture reverses hippocampal neuroplasticity alterations in aMCI. The mechanism of acupuncture’s efficacy is based on a rigorous experimental design, ensuring the reliability of the results.

The limitations of this study include the potential difficulty in implementing blinding for sham acupuncture. Additionally, due to the large number of acupuncture points used, it is challenging to identify the specific mechanisms of individual points. Moreover, given the long treatment course, there will be a considerable risk of patient dropout before completing the entire course.

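### Acupuncture in the past 4 weeks excludes aMCI patients but not healthy controls, and the thyroid items also differ, so the unrandomised baseline contrast compares groups filtered unequally

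*Protocol article*

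**What the plan says.** Section 2.4.2 (Exclusion criteria) gives a separate list for each population.

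- **aMCI patients.** Item 2 excludes "recent participation in therapeutic interventions (e.g., acupuncture or pharmacotherapy) within the past 4 weeks", and also anyone enrolled in another trial at the same time. Item 5 excludes systemic diseases associated with cognitive impairment and counts thyroid dysfunction among them only when it is untreated.
- **Healthy controls.** There are four items: disorders associated with cognitive impairment (with thyroid dysfunction named without qualification), MRI contraindications, unstable systemic conditions, and "participation in other clinical trials within the past 6 months". None mentions acupuncture or other treatment received in routine care. The inclusion criteria in section 2.4.1 do not either. They ask for "cognitive integrity confirmed by Mini-Mental State Examination (MMSE) score ≥27 and absence of subjective cognitive complaints", right-handedness and age 50-75.

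Section 2.3 gives one source for both groups: "Participants with aMCI and HCs for this study will be recruited from Shenzhen Traditional Chinese Medicine Hospital". Section 2.1 gives the role of the controls: "Healthy volunteers will serve as a comparison group for baseline comparisons". The Discussion gives the purpose of that comparison: "aMCI patients will be compared with healthy individuals to identify pathological changes in hippocampal subregions".

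**The concern.** A patient-versus-healthy contrast has no randomisation to balance background factors. It relies on eligibility rules and covariates to make disease status the main difference between the groups. Here one rule that names the trial's own intervention applies to one side only.

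The Introduction hypothesises that acupuncture improves episodic memory in aMCI by changing hippocampal subregional connectivity and volume. Those are the quantities compared at baseline. If acupuncture has some such effect outside aMCI too, a control needled for another complaint in the preceding weeks could bring that effect into the reference group, while a patient with the same history would be turned away. The exclusion of other trials does not close the gap, because it does not reach routine care.

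The thyroid items differ in a similar way. A person with treated thyroid disease can enter as a patient but not as a control, although the article itself lists thyroid dysfunction among conditions associated with cognitive impairment.

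At stake is the reading of the baseline difference as pathology, which the Discussion puts first among the study's advantages. The efficacy comparison is not at stake.

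**Working it through.** **Step 1. The two lists side by side (section 2.4.2).**

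| Feature | aMCI patients | Healthy controls |
|---|---|---|
| Acupuncture in past 4 weeks | excluded | no item |
| Pharmacotherapy in past 4 weeks | excluded, scope undefined | no item |
| Other trials | concurrent enrolment | past 6 months |
| Thyroid dysfunction | excluded if untreated | excluded without qualification |

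Both lists are printed in the article, so this is a difference between stated criteria and not a detail left to a fuller document.

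**Step 2. What the patient rule can mean.** Item 5 admits patients with treated thyroid dysfunction, who will usually be on medication. Pharmacotherapy in item 2 therefore cannot sensibly mean every drug. The acupuncture example carries no such internal limit. The firm part of the asymmetry is acupuncture; the drug part depends on a definition the article does not give.

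**Step 3. Whether the analysis removes it.** Section 2.8 names gender, age, education and total intracranial volume as imaging covariates. None captures recent acupuncture or thyroid status. The list is introduced as inclusive, so others may be intended, but none is named.

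**Step 4. Scale.** The plan has no figure to reproduce: it gives neither the share of controls recently treated nor an effect in healthy people. The following rests on assumptions.

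- Let f be the share of controls with recent acupuncture (assumed 10-30%) and e the resulting shift in their imaging measure (assumed 0.3-0.5 SD).
- Bias in the group contrast = f × e. Low end: 0.1 × 0.3 = 0.03 SD. High end: 0.3 × 0.5 = 0.15 SD.
- Standard error of a standardised difference, 150 patients v 50 controls (section 2.2): √(1/150 + 1/50) = 0.163 SD.
- Bias in standard errors: 0.03/0.163 = 0.18; 0.15/0.163 = 0.92.
- Chance of rejecting a true null at two-sided 0.05 = 1 − Φ(1.96 − bias/SE) + Φ(−1.96 − bias/SE): 5.4% at the low end and about 15% at the high end. An intermediate case, 0.2 × 0.3 = 0.06 SD, gives 6.6%.
- For an assumed true difference of 0.5 SD, a two-sample t-test has 86.1% power. If the shift narrows the gap, power falls to 81.7% (0.47 SD) at the low end and 56.9% (0.35 SD) at the high end. If it widens the gap, apparent power rises to 89.8% (0.53 SD) and 97.7% (0.65 SD).

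These rates describe one unadjusted comparison of means. The planned imaging analysis is voxel-wise with cluster-level and false-discovery-rate correction, so only the bias in SD units carries over, as an order of magnitude. No size is computed for the thyroid mismatch, because the documents give nothing to base it on.

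**The case against.** The strongest reply is that the patient rule is a washout. Patients enter a 12-week treatment comparison and should not arrive recently treated for memory complaints. Controls are assessed once, receive nothing, and must be free of cognitive complaints, so they have little reason to have had such treatment. Different roles justify different lists, and the control list is stricter in places. On this reading acupuncture for an unrelated complaint is barred in neither group, and the asymmetry largely disappears. That reading is possible and is the most coherent one for drugs. It does not settle the acupuncture part, because the text does not restrict acupuncture to cognitive indications. If that was intended, the article should say so.

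Three further objections stand as limits on size. The hypothesis concerns aMCI and a course of 36 sessions at a chosen set of points; nothing in the article says that incidental acupuncture changes the hippocampus of cognitively normal people. Recruitment at a Traditional Chinese Medicine hospital makes acupuncture in controls plausible, but nothing says that the volunteers are acupuncture patients. And a stricter thyroid rule for controls can be defended as giving a cleaner reference group, although some of the contrast could then reflect thyroid disease and not aMCI.

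A reader might also infer that patients are cleared of all treatment while controls may be on anything. The documents do not support this, since treated thyroid disease is allowed in patients.

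**Conclusion.** The point holds in a limited form. The two populations are filtered differently on recent acupuncture and on thyroid dysfunction, they meet in an unrandomised baseline contrast, and no named covariate accounts for either difference. Bias is possible, not shown. Its direction is unknown, and its illustrative size of 0.03-0.15 SD rests entirely on the assumed share of treated controls and the assumed shift; at the low end it can be ignored.

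A reader might go further and conclude that the trial's efficacy result is compromised. It is not: the verum, sham and waiting groups share one patient eligibility list and are randomised, so their comparison, including the primary AVLT-H outcome, is untouched. Severity is low. The change is worth making because it is cheap and because exposure before the baseline scan cannot be undone afterwards.

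**What to change.** In section 2.4.2:

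1. Add the 4-week acupuncture exclusion to the healthy-control list.
2. State whether the therapeutic interventions and pharmacotherapy in the patient rule mean cognition-directed treatment, and apply that same definition to both groups.
3. Reconcile the two thyroid items, or state the reason for the difference.

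For controls already scanned when the change is made, record recent acupuncture and medication in both groups and account for them in the patient-versus-healthy analysis.

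The cost is one screening question and a few volunteers deferred or replaced; the article gives no figure from which to estimate how many. Sample size does not change. The definition in item 2 also protects recruitment, since a rule read as barring any drug could exclude many controls aged 50-75.

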### Randomization, allocation concealment, and blinding

2.5

After baseline evaluation, the eligible patients of aMCI will be randomly assigned to a verum acupuncture group, a sham acupuncture group, and a waiting group. The randomly assigned sequences will be generated using SPSS. The independent research assistant will inform eligible participants of their allocation results by telephone. We could not establish the blinding of participants, acupuncturists, or intervention supervisors to the assigned treatment, but outcome assessors and data statisticians will be blind to the grouping assignment.

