#### Sham acupuncture group

2.6.2

The acupuncturist will use a placebo needle in the sham acupuncture group. The placebo needle, whose tip is blunt, is designed so that participants will have a pinprick-like sensation when it touches the skin, while the needle will not penetrate the skin and appears to be inserted (Figure 3). The same acupoints as those in the verum acupuncture group are selected for placebo needle stimulation to avoid a site-specific effect of acupuncture.

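### Section 2.5 leaves participants unblinded and tells them their allocation, contradicting the sham needle's stated purpose of controlling placebo effects and limiting unblinding

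*Protocol article*

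**What the plan says.** Section 2.5 of the protocol article randomises patients to verum acupuncture, sham acupuncture or waiting. It then states: "The independent research assistant will inform eligible participants of their allocation results by telephone". The next sentence says "We could not establish the blinding of participants, acupuncturists, or intervention supervisors to the assigned treatment", and ends by adding that "outcome assessors and data statisticians will be blind to the grouping assignment". Neither sentence treats the verum and sham arms differently from the waiting arm.

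Section 2.6.2 describes the sham as a blunt needle at the verum acupoints, built so that "the needle will not penetrate the skin and appears to be inserted". The Discussion explains why the sham is applied at those points: to imitate the verum setting, "thereby more strictly controlling the placebo effect and reducing the risk of unblinding for patients". Among its limitations it lists the following: "The limitations of this study include the potential difficulty in implementing blinding for sham acupuncture".

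The design label in section 2.1 is "This is a prospective, single-center, three-armed, parallel-designed, assessor-blinded, randomized controlled trial". The abstract says only "A randomized, controlled, blinded research will be performed".

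**The concern.** A sham needle that imitates insertion serves its purpose only if the patient does not know which needle is in use. Section 2.5 reports that participants are not blinded and that they are told their allocation. Patients in the waiting arm necessarily know they are not being needled, but nothing requires a needled patient to know the needle type.

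The stakes lie in the verum-sham contrast. The waiting arm receives no needling during observation, so verum versus sham is the only comparison that can separate needling from the expectation of being treated. The primary outcome, AVLT-H, is a word-list test that the patient performs. Patients who know they have the sham may expect less, try less hard or leave more often over 36 sessions, and the Discussion already anticipates considerable dropout. Blinded assessors protect against biased scoring, not against these differences.

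**Working it through.** **Comparing the statements.**

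| Place | What it implies for participants |
|---|---|
| Section 2.5 | Told their allocation; blinding not established; no exception for needling arms |
| Section 2.6.2 | Needle made to look inserted, which matters only if patients do not know the needle type |
| Discussion, sham rationale | Sham chosen to control placebo effects and lower the risk that patients are unblinded |
| Discussion, limitations | Blinding of the sham may prove difficult, which presumes that it is attempted |
| Section 2.1 | Claims assessor blinding only; agrees with section 2.5 |
| Abstract | Does not say who is blinded; compatible with either reading |

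The conflict is therefore section 2.5 against section 2.6.2 and the Discussion. A sham cannot lower the risk of unblinding in patients who are unblinded by design.

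**Illustration of size.** The protocol states no figure for expectation bias, so there is nothing of its own to reproduce. The inputs are:

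- n = 50 per arm (section 2.2);
- two-sided 5% level (section 2.8);
- a bias b, in SD units, between verum and sham with no true effect. This is assumed; it is not in the documents.

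Under the normal approximation, SE = √(2/n) = √(2/50) = 0.20, and

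false-positive rate = Φ(b/SE − 1.96) + Φ(−b/SE − 1.96).

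- b = 0: 5.0%
- b = 0.1: b/SE = 0.5; Φ(−1.46) + Φ(−2.46) = 0.0721 + 0.0069, about 7.9%
- b = 0.2: b/SE = 1.0; Φ(−0.96) + Φ(−2.96) = 0.1685 + 0.0015, about 17.0%
- b = 0.3: b/SE = 1.5; Φ(−0.46) + Φ(−3.46) = 0.3228 + 0.0003, about 32.3%

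With an assumed 40 completers per arm (SE = √(2/40) = 0.224), biases of 0.1, 0.2 and 0.3 SD give 7.3%, 14.6% and 26.9%.

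For scale, the difference detectable with 80% power at 50 per arm is (1.960 + 0.842) × 0.20 = 0.56 SD. All these figures are for a single unadjusted comparison; the false discovery rate adjustment in section 2.8 is not modelled.

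**The case against.** The strongest reply is that section 2.5 is loosely worded. The call may disclose only needling or waiting, and the sentence on blinding may have been written with the waiting arm and the acupuncturists in mind. The Discussion, which speaks of limiting unblinding and of difficulty in achieving blinding, fits that reading. The call script and consent text are not shown. This stands as far as it goes: the documents prove a contradiction, not what patients will hear. It does not remove the need for correction, because staff who follow section 2.5 as written could unblind the sham arm, and that cannot be undone.

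Three stronger readings are tempting, and the documents do not support them.

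- A reader might infer that the trial is simply open-label. No statement says a patient is told the word sham, and section 2.5 keeps assessors and statisticians blind.
- A reader might infer that the abstract, section 2.1, section 2.5 and the Discussion are all mutually inconsistent. Section 2.1 agrees with section 2.5, and the abstract is only unqualified.
- A reader might infer that no difference could then be attributed to acupuncture. Assessment is blinded and the outcomes include a performance test and MRI measures, so attribution would be weakened rather than lost.

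Two further objections hold. The false-positive rates follow from assumed biases, and nothing in the documents shows that biases of this size occur on a recall test with blind assessors. In addition, withholding the label may not be enough. Section 2.6.1 has verum needles manipulated to produce De qi, whereas section 2.6.2 describes only a pinprick-like feeling for the sham. Recent acupuncture is excluded only within the past 4 weeks, so some patients may recognise real needling. This is a reason to measure whether blinding worked, not a reason to disclose the arm.

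**Conclusion.** The contradiction is established from the text alone and must be resolved before patients are telephoned. The consequence is conditional: if section 2.5 is applied literally, verum versus sham is unblinded for participants, with blinded assessment and analysis, and an AVLT-H difference could partly reflect expectation, effort or uneven dropout.

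The size cannot be determined from the documents. The range of about 8% to 32% rests on an assumed bias of 0.1 to 0.3 SD, no true effect, 50 analysed per arm and no multiplicity adjustment. It shows how a modest bias would act and is not an estimate for this trial. The finding does not depend on it.

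**What to change.** Rewrite section 2.5 so that:

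- the telephone call discloses only needling or waiting;
- patients in the verum and sham arms are not told their needle type until database lock;
- patients in those two arms are described as intended to be blind to needle type, acupuncturists as unblinded, and assessors and statisticians as blind.

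Add one treatment-guess question at week 12 and report it by arm, since the difference in needling sensation may unblind some patients regardless. State in the abstract who is blinded. Section 2.1 is already consistent with assessor blinding and needs only to follow the revised description.

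If the sponsor does intend participants to know their arm, leave section 2.5 as it is and withdraw the Discussion's claim that the sham controls the placebo effect and reduces unblinding.

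The cost of the main route is revised consent and call-script wording, with neutral language about the sham, an ethics amendment and one extra question. It needs no additional patients or staff.
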